## Abstract

**Introduction:**

Screening can reduce deaths from colorectal cancer (CRC). Despite high levels of public enthusiasm, participation rates in population CRC screening programmes internationally remain persistently below target levels. Simple behavioural interventions such as completion goals and planning tools may support participation among those inclined to be screened but who fail to act on their intentions. This study aims to evaluate the impact of: (a) a suggested deadline for return of the test; (b) a planning tool and (c) the combination of a deadline and planning tool on return of faecal immunochemical tests (FITs) for CRC screening.

**Methods and analysis:**

A randomised controlled trial of 40 000 adults invited to participate in the Scottish Bowel Screening Programme will assess the individual and combined impact of the interventions. Trial delivery will be integrated into the existing CRC screening process. The Scottish Bowel Screening Programme mails FITs to people aged 50–74 with brief instructions for completion and return. Participants will be randomised to one of eight groups: (1) no intervention; (2) suggested deadline (1 week); (3) suggested deadline (2 weeks); (4) suggested deadline (4 weeks); (5) planning tool; (6) planning tool plus suggested deadline (1 week); (7) planning tool plus suggested deadline (2 weeks); (8) planning tool plus suggested deadline (4 weeks). The primary outcome is return of the correctly completed FIT at 3 months. To understand the cognitive and behavioural mechanisms and to explore the acceptability of both interventions, we will survey (n=2000) and interview (n=40) a subgroup of trial participants.

**Ethics and dissemination:**

The study has been approved by the National Health Service South Central—Hampshire B Research Ethics Committee (ref. 19/SC/0369). The findings will be disseminated through conference presentations and publication in peer-reviewed journals. Participants can request a summary of the results.

**Trial registration number:**

clinicaltrials.govNCT05408169

Strengths and limitations of this studyA suggested deadline for kit return and a faecal immunochemical test (FIT) planning tool are highly cost-effective (if effective) interventions that could be easily implemented in routine practice, through adding a sentence to the invitation letter and including a sheet of paper, respectively.A 2x4 factorial randomised controlled trial (RCT) design will allow us to test the individual and combined impact of two behavioural interventions on colorectal screening uptake.Integrating the RCT delivery into the existing colorectal screening process will provide evidence of the feasibility of providing either or both within a well-established national screening programme.Cross-sectional and qualitative evaluation research will provide further insights into the psychological mechanisms that underlie any intervention effects.While the study supports key priorities within the UK Cancer Strategies to increase uptake of FIT colorectal screening, if the interventions are effective, this will lead to an increase in demand on follow-up colonoscopy which currently has limited capacity.

## Introduction

Colorectal cancer (CRC) is the second leading cancer killer in Scotland and worldwide.^1 2^ Screening has been shown to reduce deaths from CRC if enough people invited to participate.^3 4^ The challenge is that high uptake is hard to achieve, and remains persistently below the target levels internationally. For example, screening rates are 44% in Australia and 62% in the USA.^5 6^ Following the introduction of the single-sample faecal immunochemical test (FIT) in 2017, screening uptake in Scotland has risen to 65%, thus exceeding the Scottish target rate of 60%,^7^ but remains just below the internationally accepted European Union target uptake rate of at least 66%.^8^ Although this is higher than the European population-based CRC screening programmes average of 25%,^8^ one-third of the population still do not screen and uptake is unevenly distributed across socioeconomic factors leading to health inequalities.^7^

### Theoretical rationale

CRC screening uptake remains suboptimal, despite high levels of public enthusiasm. In a Scottish survey, 85% of people reported intending to complete the FIT,^9^ yet participation is 65%.^7^ This suggests that apparent enthusiasm for the new FIT is not being translated into uptake. A major reason for this disparity may be that people are ‘not getting round to it’,^10^ reflecting the well-recognised intention-behaviour gap and consistent with the observation that much of our behaviour is determined by factors other than conscious, deliberative control.^11–14^ This disparity is consistent with previous work on ‘inclined abstainers’,^13^ showing that a proportion of people are inclined to participate in screening but fail to do it. This explanation seems particularly likely for CRC screening which, unusually for a screening test, is self-completed at home. General open-ended intentions to act often fail to lead to the desired behaviour.^15^ Our previous research has found that people often put off or forget to complete and return the FIT.^16^ Additional support through prompting the setting of FIT completion goals and planning may better support participation among those inclined to complete the FIT but who might otherwise fail to act.

#### Goal setting

Goal setting, and particularly action-planning, can help initiate behaviour in those inclined to act. This is achieved by prompting a person to specifically plan when, where and how to act, which lessens the decision-making burden when that situation is encountered.^17–19^ For example, a suggested deadline by which a task should be completed may prompt action planning. Currently, CRC screening invitations in Scotland provide detailed information about ‘where’ and ‘how to act’ but ‘when to act’ is left open, potentially reducing the likelihood that recipients will plan and act accordingly. In breast and cervical screening, providing a fixed appointment time increased uptake compared with an open invitation.^20^ Similarly, in our recent qualitative study, women who attended breast and cervical screening but had not completed CRC screening described how the lack of an appointment facilitated the delay and forgetting of CRC screening: ‘If it’s a bowel screening one, yep, put it somewhere and think “Yes, I’ll do that” and then forget about it because it doesn’t have an appointment date. I think if something has an appointment date, you’re forced to act’ (54 years, not screened for CRC).^16^
^p6^ Recent evidence suggests that both short (1 week) and long (3 week) deadlines achieve small but significant increases in FIT return.^21^ Optimal deadline length, however, has yet to be determined. It is important to establish if a suggested deadline for FIT kit return can increase CRC screening participation compared with an open invitation in a population-based screening programme.

#### Planning support

Systematic reviews clearly demonstrate that interventions supporting people to plan how to enact a behaviour (including action and coping planning) are particularly suited to changing the behaviour of inclined abstainers.^12^ Indeed, planning support interventions have been shown to be more effective than other approaches, such as self-monitoring or providing instructions,^22^ and have high adherence rates.^23^ Planning interventions are often based on implementation intentions which promote behaviour change using ‘if-then’ plans and have successfully reduced alcohol consumption and smoking, and increased cancer screening attendance and physical activity.^11 12 24 25^ Previous research on implementation intention interventions for CRC screening has had limited success when it has relied on prepared statements of barriers (‘if’) and possible solutions (‘then’).^26^ Encouraging people to form their own implementation intentions for CRC screening appears to produce clinically significant increases in uptake.^24^ Planning tools (also called volitional help sheets) emphasise this by requiring users to physically draw a line to link a barrier, for example, ‘If I am tempted to eat when I am anxious’ with a solution for example, ‘then I will reward myself when I do not overeat’ to ensure user-engagement.^27^
^p706^ The rationale is that the ‘if’ barriers or critical situations are made personalised and salient and, as a result, the ‘then’ response or solution comes automatically to mind.

The Medical Research Council’s recently updated guidance on complex intervention development and evaluation recommends addressing questions beyond intervention effectiveness, such as ‘whether and how the intervention will be acceptable, implementable, cost effective, scalable, and transferable across contexts’.^28^
^p2^ With a view to implementing a suggested deadline or planning tool at national scale, if effective, the acceptability of both interventions to CRC screening service users must be investigated.

### Objectives

The overall aim of the TimE fraMe and Planning tOol (TEMPO) study is to evaluate the impact of a suggested deadline and planning tool on FIT return in the Scottish Bowel Screening Programme.

The study addresses six research questions:

Does providing a suggested deadline increase uptake of CRC screening?Does providing a FIT planning tool increase uptake of CRC screening?Does providing both a suggested deadline and a FIT planning tool increase uptake of CRC screening?Does the length of the suggested deadline (1, 2 or 4 weeks) impact on uptake of CRC screening?What are the cognitive and behavioural mechanisms underlying any observed effect of providing a suggested deadline, a planning tool or a combination of both?How acceptable do participants find receiving a suggested deadline, a planning tool or a combination of both?

## Methods and analysis

The study employs a 2×4 factorial randomised controlled trial (RCT) design combined with cross-sectional quantitative and qualitative evaluation research with a subsample of trial participants. Figure 1 shows the Consolidated Standards of Reporting Trials flow chart.

**Figure 1 F1:**
[figure not shown]
CONSORT flow chart. CONSORT, Consolidated Standards of Reporting Trials; FIT, faecal immunochemical tests.

### Study setting

This is a single-centre trial to be conducted in collaboration with the Scottish Bowel Screening Centre based in Dundee, Scotland, and integrated into the national CRC screening programme. In Scotland, colorectal screening is offered to people aged 50–74, every 2 years, by single-sample FIT.

### Eligibility criteria

All people eligible for CRC screening in Scotland who have a Community Health Index Number can be included in this study.

### Recruitment and allocation

Following established recruitment procedures,^29 30^ working in partnership with the Scottish Bowel Screening Centre staff, 40 000 consecutive adults due to be sent an FIT will be randomised to one of eight groups (figure 1) from 20 June 2022 over approximately 10 days.

The randomisation schedule will be computer-generated at the Robertson Centre for Biostatistics, University of Glasgow. The schedule will be stored in a secure area of the Robertson Centre for Biostatistics network, with no access for those developing the statistical analysis programmes and transferred via a secure web portal to the Scottish Bowel Screening Centre team, who identify when people are to be invited for CRC screening. The IT system electronically generates the appropriate mailing packages to be sent out to each person. For this study, randomisation will be performed by the method of randomised permuted blocks of length 8, so that in every eight packages sent, exactly one of each type will be included.

### Blinding

The process of generating and mailing the routine screening invitation letters is fully automated and is conducted by a large mail-handling company. A data file containing contact details for the screening invitation letters is sent to the mail-handling company daily. The company will print screening invitation letters with suggested deadlines and add the planning tool in accordance with the participants’ allocation within this study. The researchers, including those performing the analysis, will therefore be blind to the allocation of participants. The participants will not be informed of the experiment.

### Interventions

There will be eight allocation groups (figure 1): group 1—standard invitation (n=5000); group 2—1 week deadline (n=5000); group 3—2 week deadline (n=5000); group 4—4 week deadline (n=5000); group 5—planning tool (n=5000); group 6—planning tool plus 1 week deadline (n=5000); group 7—planning tool plus 2 week deadline (n=5000) and group 8—planning tool plus 4 week deadline (n=5000).

#### Deadline intervention

Those allocated to the deadline intervention (groups 2–4 and 6–8) will receive a screening invitation letter with one of three suggested deadlines added (table 1): 1 week, 2 weeks and 4 weeks. This choice was based on feedback from the Cancer Research UK Early Diagnosis Advisory Group, public and patient involvement representatives and observation of kit return patterns in the Scottish Bowel Screening Programme. The deadline will be displayed centrally on the standard CRC screening invitation letter as a bold, highlighted sentence (table 1). The wording *or as soon as possible* is intended to make clear that the deadline constitutes a suggested return date only, to avoid discouraging participants who are unable to meet the deadline. The existing invitation letter already states *post it as soon as possible* and the suggested deadline builds on this by providing a more explicit and specific goal. Furthermore, a standard reminder will be sent after 6 weeks without a deadline and so will provide a safety net for any potential participants who have missed the deadline in their first invitation letter.

**Table 1 T1:** Deadline intervention arms

Intervention group	Suggested FIT return deadline	Deadline sentence
Groups 2 and 6	1 week deadline	**Please return your kit within 1 week (by [insert date 10 days from posting date]) or as soon as possible.**
Groups 3 and 7	2 week deadline	**Please return your kit within 2 weeks (by [insert date 17 days from posting date]) or as soon as possible.**
Groups 4 and 8	4 week deadline	**Please return your kit within 4 weeks (by [insert date 31 days from posting date]) or as soon as possible.**

FIT, faecal immunochemical test.

#### Planning tool intervention

Those allocated to the planning tool intervention (groups 5–8) will receive a planning tool with their screening invitation. The planning tool will be presented on a separate single sheet of paper inserted into the CRC screening invitation envelope. It asks participants to identify *concerns* (ie, barriers) they have with using the FIT from a list and to link them to a *tip* (ie, solution) from an adjacent list to help them overcome this concern. The planning tool reads, *Here are some tips that people find helpful to make the bowel screening kit even easier. Try drawing a line from any concern you have to a tip which might help you. You can draw as many or as few lines as you like. There are no right or wrong answers.* In conventional planning tool designs, concerns reflect critical situations and tips reflect solutions.^27^ Each concern and tip is accompanied by an image illustrating its meaning. Finally, participants will have the option to write their own concern or tip. While the planning tool instructions encourage people to use the planning tool, they do not suggest that participants must do so in order to take part in CRC screening. The specific listed concerns and tips are based on extensive development work involving consideration of existing theoretical and empirical literature, in-depth qualitative interviews, a survey of people who had been invited to complete a FIT and codesign workshops to create a user-friendly planning tool with members of the public who have completed the FIT and others who have not completed the FIT.^31–33^ The final planning tool was reviewed and approved by the Research Team, Patient and Public Involvement representatives (PPRs), and a patient and public group of the Scottish Primary Care Network.

Table 2 displays the concerns and tips shown in the planning tool. The planning tool is presented in online supplemental file 1.

10.1136/bmjopen-2022-066136.supp1Supplementary data

**Table 2 T2:** Planning tool intervention—concerns and tips

Concerns	Tips
If I feel scared about bowel screening…	… then I’ll read the instructions.
If I keep putting off using the kit…	… then I’ll think that this kit could help save my life.
If I am not used to using a kit like this…	… then I’ll put the kit by the toilet to remind me.
If I am worried what it might find…	… then I’ll wash my hands after using the kit.
If I think using the kit is messy…	… then I’ll tell myself that I’m responsible for my health.

#### Control group

As the trial has a factorial design, it follows that the control group for the assessment of the independent effect of each intervention is all those who did not receive the intervention. This is because any impact of one intervention impacts to an equal extent those who do and do not receive the other intervention. Therefore, groups 1 and 5 together make up the control group for the assessment of suggested deadlines and groups 1–4 make up the control group for assessment of the planning tool. Only participants in group 1 will be sent a standard CRC screening invitation and FIT (without a suggested deadline or a planning tool) according to normal current practice. It is also important to note that three groups will receive both a planning tool and a suggested deadline, which will allow assessments of the combined effects of a suggested deadline and the planning tool compared with receiving a deadline only, a planning tool only or neither.

### Evaluation research of cognitive and behavioural mechanisms and acceptability

We will conduct two studies answering research questions 5 and 6.

#### Questionnaire survey

We will conduct a questionnaire-based case–control study to assess the cognitive and behavioural mechanisms underlying any effect of providing a suggested deadline for FIT kit return and a planning tool.

##### Recruitment

At least 3 months after the screening invitation, a subsample of trial participants will be identified from all eight groups, including people who returned (case) and did not return (control) their FIT, and people living in 40% most and least deprived neighbourhoods (based on Scottish Index of Multiple Deprivation (SIMD) quintiles).^34^ The subsample will be sent a postal invitation to complete and return a survey. The aim is to obtain responses from approximately 1000 cases and 1000 controls across the eight groups. Based on previous work, we anticipate achieving a higher response rate from those returning the FIT and a lower response from those not returning the FIT, therefore approximately 11 872 questionnaires will be mailed, as shown in figure 1.^32^ A reminder questionnaire will be sent to those who have not returned the questionnaire after 3 weeks.

##### Materials and procedure

A brief questionnaire will include items to assess cognitive and behavioural mechanisms, for example, action and coping planning,^17^ that were previously adapted for the CRC screening context.^19 32^ It will also include a theory-informed acceptability measure that has been subject to a prevalidation method but does not yet have fully established psychometric properties,^35^ as well as demographic characteristics. Participants will be asked if they are willing to participate in future research to assist recruitment for qualitative interviews.

#### Qualitative interviews

We will conduct a qualitative interview study, adopting a phenomenological approach to explore participants’ experiences of receiving an FIT with and without the interventions, and explore acceptability of the interventions.

##### Recruitment

Interview participants will be sampled from survey participants who have indicated willingness to participate in further research. We will recruit approximately 40 participants and will aim to achieve a balance of participants who have and have not returned the FIT, men and women, from across the CRC screening invitation age range (50–74 years), from both deprived and affluent neighbourhoods (based on SIMD) and from the trial intervention groups. The estimated sample size is based on the principles of achieving data saturation and what is pragmatic, yet informative.

##### Procedure

Potential participants will be contacted to request participation in a semistructured qualitative interview conducted face-to-face, by telephone or video-call. Interviews will last approximately 30–60 min, and topic guides (online supplemental file 2) will be used. Participants will be offered £30 towards travel and expenses.

10.1136/bmjopen-2022-066136.supp2Supplementary data

### Outcomes

Our primary outcome is the proportion of FITs returned correctly completed to be tested by the CRC screening laboratory providing a positive or negative result, within 3 months of the FIT being sent to a person. The return and successful testing of any replacement FITs that were sent to people after the first FIT at study baseline will be treated as a FIT return. As secondary outcomes, we will evaluate cognitive and behavioural mechanisms and explore the acceptability of both interventions.

### Sample size

This 2×4 factorial RCT involves the assessment of two interventions, so each will be assessed at a significance level of 2.5%, to preserve an overall Type I error rate of 5%.

The assessment of the effect of the planning tool will involve the comparison of two groups of 20 000 participants. At a significance level of 2.5%, this gives 90% power to detect an increase in uptake rates from 65% to 66.8%. Alternatively, if the intervention increases uptake rates from 65% to 68%, the 97.5% CI for the difference in uptake rates will have a width of±1.06%.

The assessment of the effect of suggested deadlines for FIT kit return will involve four groups of 10 000 participants. Comparing each suggested deadline with the control group (no deadline) at a significance level of 0.83% (one-third of 2.5%), there will be 90% power to detect increases in uptake rates from 65% to 67.63%. If an intervention increases uptake from 65% to 68%, the 99.17% CI for the difference in uptake rates will have a width of±1.76%.

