#### Primary outcome

The primary analysis will use a logistic regression model, including a binary variable for whether the planning tool was provided, and a four-level categorical variable denoting which deadline was suggested. Age, sex and area deprivation (measured by the SIMD^34^) will be included in the model, to improve model specification. The main effects of each intervention will be reported as an OR, with a CI and p-value. For the estimate of the effect of the planning tool, a 97.5% CI will be reported. For estimates of the effect of alternative suggested deadlines, relative to no deadline, 99.17% CIs will be used. Subsequent analyses will model the interaction between the two interventions, to assess whether the interventions have independent effects or are synergistic. We shall also model interactions between each intervention effect and age, sex and deprivation, to assess whether the interventions have different effects for subgroups of the population. Assessing uptake by deprivation is important given the disparities in screening uptake by deprivation (53% most deprived vs 73% least deprived);^7^ which any intervention could reduce or exacerbate.^36^

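### The fixed Bonferroni levels are valid but discard the level of every rejected hypothesis; weighted Holm with the same starting levels would gain power at no cost in error, by an amount that depends mainly on whether the planning tool works

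*Protocol article*

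**What the plan says.** Under Sample size, the protocol article divides the 5% equally between the two interventions: "each will be assessed at a significance level of 2.5%, to preserve an overall Type I error rate of 5" per cent. The planning tool is one comparison of 20 000 with 20 000. The deadline factor gives three comparisons with no deadline, each "at a significance level of 0.83% (one-third of 2.5" per cent). The section Control group makes the comparator common to all three: "groups 1 and 5 together make up the control group for the assessment of suggested deadlines", that is, 10 000 people.

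The stated power for each deadline is that "there will be 90% power to detect increases in uptake rates from 65% to 67.63" per cent. For the tool, "this gives 90% power to detect an increase in uptake rates from 65% to 66.8" per cent.

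The Primary outcome paragraph of the data analysis plan carries the same levels into reporting: "For the estimate of the effect of the planning tool, a 97.5% CI will be reported", and "For estimates of the effect of alternative suggested deadlines, relative to no deadline, 99.17% CIs will be used". The article describes no reallocation of a level after a rejection.

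**The concern.** The four primary hypotheses (tool; 1, 2 and 4 weeks) are tested by an unrecycled weighted Bonferroni rule. The rule is valid, but a uniformly more powerful one exists with the same starting levels. If the tool is clearly effective, its 2.5% has done its work and could pass to the deadlines, and the reverse. Under the fixed rule it is discarded.

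The deadlines carry the strictest level. The article wants a verdict on each length, since research question 4 asks whether 1, 2 or 4 weeks matters and the Introduction expects small effects from deadlines. A deadline that works, but by less than the planned 2.63 points, could be left non-significant when a rule with the same 5% error would have declared it.

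**Working it through.** **Inputs.** Eight cells of 5000 (Interventions); 20 000 v 20 000 for the tool and 10 000 v 10 000 for each deadline; base uptake 65%; levels 2.5% and 0.83% (Sample size). Sidedness is not stated. Two-sided tests are assumed, because the stated interval levels match the test levels and the deadline figures reproduce that way.

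**The plan's own figures.**

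- Total level: 0.025 + 3 × 0.00833 = 0.05, as claimed.
- Deadline power, 65% v 67.63%, two-sided 0.83% (z = 2.638). Pooled p = 0.66315. Null SE = √(2 × 0.66315 × 0.33685 / 10 000) = 0.006684. Alternative SE = √((0.65 × 0.35 + 0.6763 × 0.3237) / 10 000) = 0.006682. Power = Φ[(0.0263 − 2.638 × 0.006684) / 0.006682] = Φ(1.297) = 90.3%. The stated 90% reproduces.
- Interval half-widths at 65% v 68%: tool 2.241 × √(0.4451 / 20 000) = 1.06%; deadline 2.638 × √(0.4451 / 10 000) = 1.76%. Both reproduce.
- Tool, 65% v 66.8%, two-sided 2.5%: the same formula gives 94.0%, above the stated 90%. The mismatch is conservative and does not bear on this point.

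**What reallocation does.** Start with weights 1/2, 1/6, 1/6, 1/6 of 5%. After each rejection, rescale the remaining weights to sum to 1.

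- Tool rejected: each deadline moves from 0.83% to 5%/3 = 1.67%. One further rejection gives 2.5% each for the remaining two; a second gives 5% for the last.
- Tool not rejected, one deadline rejected: remaining weights sum to 5/6, so the tool moves to 3% and the other two deadlines to 1%.
- Tool not rejected, all three deadlines rejected: the tool moves to 5%.

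The first step is the plan's own rule, so no rejection can be lost. For scale, the uptake detectable with 90% power at 10 000 per group is 67.62% at a level of 0.83%, 67.46% at 1.67% and 67.17% at 5%.

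**Simulation.** 400 000 replicates of the 2×4 design with additive risk differences and stratified Wald tests. Each entry is fixed levels → weighted Holm, in per cent. The +2.63 and +1.8 points are the article's design effects. The +2.0 is an assumption that shows what happens below them.

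| Tool | Deadlines | Each effective deadline | All three | At least one |
|---|---|---|---|---|
| +1.8 | all +2.63 | 90.8 → 96.9 | 79.6 → 93.6 | 98.7 → 99.3 |
| +1.8 | one +2.63 | 90.7 → 94.0 | | |
| none | all +2.63 | 90.3 → 92.1 | 78.7 → 83.3 | 98.5 → 98.5 |
| none | one +2.63 | 90.23 → 90.35 | | |
| +1.8 | all +2.0 | 64.4 → 79.6 | 40.1 → 67.0 | 86.2 → 91.2 |
| +1.8 | one +2.0 | 64.3 → 72.6 | | |
| none | all +2.0 | 63.6 → 67.0 | 39.1 → 46.1 | 85.9 → 86.0 |
| none | one +2.0 | 63.5 → 63.8 | | |

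**Family-wise error under weighted Holm.**

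- Global null: 4.79%.
- Tool +3.0, all three deadlines null: 4.45%.
- Tool +3.0, two deadlines null, the third +3.0: 4.55%.
- Tool +3.0, one deadline null, the other two +3.0: 4.80%.
- Tool null, all deadlines +4.0: 5.01%, with Monte Carlo standard error √(0.05 × 0.95 / 400 000) = 0.034 points.

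All are consistent with control at 5%.

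**Effect on the intervals.** A hypothesis rejected only through reallocation has, by definition, a p-value above its starting level. A deadline declared at 1.67% but not at 0.83% has a p-value between the two, so its matching 99.17% interval includes an odds ratio of 1. This applies to every added rejection, for any interval that corresponds to the test.

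**The case against.** The strongest reply is that nothing here is wrong. The levels sum to 5%, the deadline power reproduces, and fixed levels have a coherent purpose: each test agrees with its reported interval, and the four intervals together cover at 95% or better. The article also justifies its sample size partly by interval width. Preferring that agreement to extra rejections is legitimate, and step-down would break it for the whole of the gain. All of this stands. It limits the point to a missed improvement and means that the reporting rule must change along with the test.

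The second reply is that the gain is selective. This also stands. The large figures need an effective tool, and the largest also needs deadline effects of 2.0 points, which is not a planning value in the article. With a null tool the gain is small. The chance of finding at least one deadline at the design effect barely moves.

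The third reply is that a condensed article may leave a step-down rule to the analysis plan. That is possible: the article fixes the starting levels and the intervals but does not exclude such a rule.

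A reader might infer that the plan fails to control error or is underpowered for deadlines, or that step-down raises deadline power substantially whatever the truth. The article's own figures contradict the first, and the null-tool rows contradict the second.

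**Conclusion.** The point holds as a cheap, optional improvement, not as an error. Weighted Holm with the same starting levels dominates the fixed rule in rejections at the same 5%. At the design effects for the tool and all three deadlines, it adds about 6 points of power per deadline and 14 points for declaring all three. With all deadlines at +2.0 it adds about 15 and 27 points. With a null tool the gain per deadline falls to 2 to 3 points if all deadlines work and 0.1 to 0.3 if one does.

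These results assume two-sided tests, 65% base uptake, additive effects and no covariates. The adjusted logistic model should give very similar results. Reallocation does not itself compare deadline lengths with each other.

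**What to change.** Before unblinding, state that the four primary hypotheses are tested by weighted Holm at an overall 5%, with starting levels 2.5%, 0.83%, 0.83% and 0.83%, and with the level of each rejected hypothesis reallocated in proportion to the remaining weights. Report multiplicity-adjusted p-values: order the hypotheses by p/w, multiply each p/w by the sum of the weights not yet rejected, take the running maximum (capped at 1), and compare with 5%.

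Keep the 97.5% and 99.17% intervals, described as fixed-level simultaneous intervals. Amend the Primary outcome paragraph to say that significance is judged by the adjusted p-value and not by those intervals, because any hypothesis rejected only through reallocation will have an interval that includes an odds ratio of 1.

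The cost is about one paragraph plus that reporting sentence, and the loss of one-to-one agreement between test and interval. Sample size, data collection and interventions do not change. If the analysis plan already contains a step-down rule, confirm it and align the interval wording.

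### The planning-tool power statement does not follow from its own inputs: 20,000 per group at 2.5% gives 94% power for 65% versus 66.8%, and the 90%-power rate is 66.7%

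*Protocol article*

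**What the plan says.** All the relevant statements are in the protocol article.

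- **Significance level.** The Sample size section splits the error rate between the two interventions: "each will be assessed at a significance level of 2.5%, to preserve an overall Type I error rate of 5" per cent.
- **Group size.** In the same section: "The assessment of the effect of the planning tool will involve the comparison of two groups of 20 000 participants".
- **Power.** The sentence at issue reads "At a significance level of 2.5%, this gives 90% power to detect an increase in uptake rates from 65% to 66.8" per cent.
- **Precision.** For a rise from 65% to 68%, "the 97.5% CI for the difference in uptake rates will have a width of±1.06" percentage points.
- **Deadlines.** With 10,000 per group and a level of 0.83%, "there will be 90% power to detect increases in uptake rates from 65% to 67.63" per cent.
- **Reporting.** The Primary outcome part of the data analysis plan states: "For the estimate of the effect of the planning tool, a 97.5% CI will be reported".

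The document does not say in words whether the tests are one- or two-sided. Pairing a 2.5% level with a 97.5% interval implies two-sided.

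**The concern.** The planning-tool sentence gives a level, a group size, a power, a control rate and a detectable rate. Any four of these determine the fifth, and the five as printed are not compatible. The deadline figure and the interval widths in the same section do agree with their own inputs, so the mismatch cannot be put down to an unusual method used throughout.

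This is the power statement for one of the two primary comparisons. As printed, it understates power and overstates the smallest effect the comparison can detect with 90% power. A reader who checks it also cannot tell whether the detectable rate is a slip or whether a level other than 2.5% was used. The second possibility matters because the protocol's control of the overall 5% error rate rests on 2.5% per intervention.

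**Working it through.** **Inputs** (Sample size section): control rate p1 = 0.65; n = 20,000 per group, 1:1; two-sided α = 0.025, so z = 2.2414; power 90%, so z = 1.2816.

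**Formula.** Two-proportion z test, variance pooled under the null:

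- p̄ = (p1 + p2)/2
- SE0 = √[2·p̄(1 − p̄)/n]
- SE1 = √[(p1(1 − p1) + p2(1 − p2))/n]
- power = Φ[(p2 − p1 − z·SE0)/SE1]

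**Step 1. Reproduce the plan's neighbouring figures.**

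- Planning-tool interval, 65% versus 68%: 2.2414 × √[(0.65·0.35 + 0.68·0.32)/20,000] = 2.2414 × 0.0047175 = 0.01057, or ±1.06 points. This agrees with the plan and confirms both 20,000 per group and the two-sided 2.5% level for this comparison.
- Deadline interval, 10,000 per group, α = 0.025/3 (z = 2.6383): 2.6383 × 0.0066716 = 0.01760, or ±1.76 points. This agrees.
- Deadline detectable rate at 90% power: 67.62%, or 67.63% with a continuity correction, against 67.63% stated. Power at 67.63% is 90.3%. This agrees.

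**Step 2. Power at the stated planning-tool rate, p2 = 0.668.**

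- p̄ = 0.659, SE0 = 0.0047405, SE1 = 0.0047396
- (0.018 − 2.2414 × 0.0047405)/0.0047396 = 1.556
- Φ(1.556) = 0.940

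Power is 94.0%, not 90%.

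**Step 3. Solve for the rate with 90% power.** The solution is p2 = 0.66671, or 0.66676 with a continuity correction; both round to 66.7%. Power at exactly 66.7% is 91.0%.

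**Step 4. What would make 66.8% correct?**

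- Group size: n = [2.2414·√(2·0.659·0.341) + 1.2816·√(0.65·0.35 + 0.668·0.332)]²/0.018² = 17,215 after rounding up (17,325 with a continuity correction). That is about 14% below 20,000.
- Significance level: two-sided α of about 0.0119 gives 90% power at 66.8% with 20,000 per group.

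**Step 5. Does another reading rescue the figure?**

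| Variant at 20,000 per group | Power |
|---|---|
| Pooled, 2.5% two-sided, p2 = 66.8% | 94.0% |
| Unpooled variance | 94.0% |
| Arcsine | 94.0% |
| Log-odds | 94.0% |
| Continuity-corrected | 93.9% |
| 2.5% one-sided | 96.7% |
| Rounding, p2 = 66.75% | 92.6% |
| Rounding, p2 = 66.85% | 95.2% |
| 1.25% two-sided, p2 = 66.8% | 90.3% |

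Of these, only a two-sided level of 1.25% brings the result close to the printed one (detectable rate 66.79%). The protocol assigns that level to nothing. It would be consistent with 2.5% having been halved once too often, but that is inference.

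**The case against.** The case against giving this much weight is sound in several respects.

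- **The error is on the safe side.** Read as a floor, 90% power at 66.8% is met, since the actual power is 94%. Nobody would be led to think an inadequate trial adequate.
- **The figure does not drive the design.** The section takes the group sizes as given and reports what they yield. The more demanding comparison, the deadlines with 10,000 per group at 0.83%, has a figure that reproduces. No sample size, significance level, model or interval depends on 66.8%.
- **A correct measure sits beside it.** The ±1.06-point half-width already tells the reader how precise the planning-tool comparison is.
- **The method is not stated.** Software, test and sidedness are not given, and the plain formula gives 67.62% rather than 67.63% for the deadlines, so the exact procedure is not established.

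The first three points limit the consequences but do not make the sentence right. The section reports what the design gives, and this report is wrong; the floor reading also sits badly with a deadline figure quoted to two decimals at its 90% value. The fourth point does not help either: every standard variant at 2.5% gives 93.9% power or more at 66.8%. The deadline sentence is not a second instance of the error. It serves only as a check on the method.

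**Conclusion.** The concern holds. At the stated inputs the planning-tool comparison has 94.0% power for 65% versus 66.8%, so the type II error there is 6.0% rather than 10%. The difference detectable with 90% power is 1.67 points rather than 1.8, a discrepancy of 0.13 point.

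The conclusion assumes a two-sided 2.5% test, which is inferred from the paired 97.5% interval and supported by the reproduced ±1.06. A one-sided reading would widen the gap. It also assumes the full 20,000 per group with no allowance for loss or clustering; the section mentions neither, and its interval width uses the full number.

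The error is modest, conservative and confined to one sentence. It calls for a correction, not for any change to the trial.

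**What to change.** Replace the detectable rate or the power in the planning-tool sentence, so that it reads either 90% power for a rise from 65% to 66.7%, or 94% power for a rise from 65% to 66.8%. The first option keeps the sentence parallel with the deadline statement.

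Before doing so, check the original calculation and confirm that two-sided 2.5% is the level intended for this comparison, and say in the text that the tests are two-sided. If a different level turns out to have been used, the sentence should be recalculated at 2.5%, the level on which the error-rate split and the 97.5% interval are based.

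The cost is one number and a short clarification. Sample size, randomisation, analysis model and reported intervals stay as they are.
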